### Interim analysis

We will conduct an interim analysis at 6 months. Testing the measurements, questionnaires, response rate, and other study materials are the main objectives of this analysis. It will be used to evaluate the attrition rate, trends, and any difficulties or negative outcomes associated with the administration of the intervention. This analysis would not be reported as a result. The 12-month analysis is the final one.

### Data management

Two trained research assistants will gather data under the supervision of a research specialist. In sealed envelopes, all collected data will be delivered to a bio-statistician who will not be involved in any of the research activities and will be unaware of each participant’s assignment. All data must be entered twice, according to institutional regulation. The bio-statistician will clean and analyze the data. Stata version 16 (Stata corp SE) and R (version 4.0.3) will be utilized for all kinds of analysis in this study.

The research staff involved in data collection will include two research assistants and one research specialist. Two research assistants, in partnership with local hospital staff and under the supervision of a research specialist, will collect the data. A 2-day on-site training of research assistants on hypertension and its control, treatment, and how to respond to common questions about blood pressure and medication adherence including medication side effects will be conducted using a standard training module developed by a team of specialists from one of the study hospitals. They will also provide counseling and support to participants in filling out surveys. Data collection and randomized controlled trial procedure guidelines will be covered in three training sessions.

Each participant will receive a 5-min personal consultation to assist them in filling out the questionnaire, measuring their blood pressure, and counting their pills. Systolic blood pressure will be recorded by a nurse who will be oblivious to the study participants’ group. MODEL-605P YAMASU, a calibrated upper-arm mercury sphygmomanometer, will be utilized for this purpose. The blood pressure of the participant will be measured according to conventional procedures. Within 5 min, two different readings will be collected, with the average measurement being the final measurement. If the difference between the two measures is greater than 5 mmHg, a third evaluation will be performed, with the average of the two closest measurements being used as the final measurement.

Each of the participants will be given a paper-based questionnaire. Interviewers will read the questions to the participants and note down their answers if they have difficulty filling out the response. The paper-based questionnaires “Self-efficacy for Appropriate Medication Adherence Scale” (SEAMS) [34] contain socio-demographic, health-related, and adherence-related validated questions that would be employed in Urdu and English. The SEAMS is a 13-item measure for evaluating medication self-efficacy in chronic disease management that looks to be appropriate for people with low literacy abilities [34]. This survey used a three-point response system, with 1 indicating lack of confidence, 2 indicating moderate confidence, and 3 indicating extreme confidence. The 13-item scale had a range of possible scores from 13 to 39. In terms of drug adherence, greater ratings indicated higher levels of self-efficacy and vice versa. It is a dependable and precise device. Principal component factor analysis was used to determine the study’s validity. The researchers established a two-factor solution that accounted for 52.3% of the variance. Test-retest reliability had a moderate level of dependability (Spearman’s *r* = 0.62, *p* = 0.001). Internal consistency (Cronbach’s alpha = 0.89) is good [34].

The participants will be asked how many tablets they were prescribed for the period in question, as well as how many pills they took and missed during that time. Adherence rates will be calculated by dividing the number of pills ingested during a period by the number of tablets suggested for that period. Based on past research, an 80% cut-off value has been developed. Non-adherents will account for less than 80% of the rate, while adherents will account for more than 80% [7].

At the end of the sixth and twelfth months, participants who completed the baseline survey in all four groups will be invited to one of the study institutes to be questioned by qualified interviewers or over the phone who will be unable to come to complete the second round of blood pressure measurement, SEAMS filling, health-related quality of life post-intervention using EQ-5D-3L and EQ-VAS, and pill-counting information (Table 2).

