## Methods

### Study design

It is a factorial randomized controlled trial with a superiority design and a double-blinding approach. Intention-to-treat analysis with 12 months of follow-up will be applied to determine the efficacy of Ed-counselling assistance and mHealth intervention on hypertensive patients at four teaching hospitals in Lahore, Pakistan. Lahore is the provincial capital of Punjab (the largest province in the country) [21]. It is the world’s eighteenth-largest city and Pakistan’s second-largest metropolis. The SPIRIT 2013 Statement (Standard Protocol Items: Recommendations for Interventional Trials) [22] provides the basis for this research. A factorial approach will be used to assign participants to the four groups. The groups will receive standard care, Ed-counselling, mHealth intervention, and combined intervention (Fig. 1). All groups will be followed up for a period of total 12 months. Systolic blood pressure, the Self-efficacy for Appropriate Medication Adherence Scale (SEAMS), the number of prescribed tablets taken for a specified period (self-reporting), and health-related quality of life will be measured at least three times: at baseline, 6 months, and 12 months after the intervention [23, 24].

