#### Educational support with peer counseling

Peer counseling sessions will be led by doctors who are specialized in hypertension. Patients and their families will be focused on these sessions. Face-to-face sessions will take roughly 20–25 min each. Patients will receive spoken and written instructions based on their abilities during these sessions. Counseling sessions are geared toward overcoming both general and personal obstacles. They will learn about the need of adhering to medicine, nutrition, and exercise regimens, as well as about the possible consequences of failing to do so (heart attack, stroke, nephropathy, retinopathy, and dementia). The counseling component also addresses personal barriers to taking medication and is designed to assist participants in better understanding their drug-taking attitude. The peer counseling sessions will take place four times for a total of twelve months, at 1, 4, 8, and 12 months. Information on hypertension, blood pressure self-monitoring, and frequent systolic blood pressure tests, as well as body weight and serum cholesterol values, are included in the instructional support. Food control, exercise therapy, hypertension problems, and their management will also be explored as non-pharmacological therapeutic approaches. Furthermore, based on their unique needs, patients will be informed about medicine administration timings and quantities. Finally, all patients will be informed about antihypertensive medications, including indications, side effects, contraindications, warnings/precautions, drug interactions, and pregnancy risks. Educational components will be delivered through educational booklets with animated infographics.

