### Outcome measures

The primary outcome measure is the change in participants’ systolic blood pressure at 0, 6, and 12 months. It will be recorded by a nurse who will be oblivious to the study participants’ group. MODEL-605P YAMASU, a calibrated upper-arm mercury sphygmomanometer, will be utilized for this purpose. The blood pressure of the participant will be measured according to standard procedures. Two different readings will be collected within 5 min; the average measurement will be the final measurement. If the difference between the two measures is greater than 5 mmHg, a third evaluation will be performed, with the average of the two closest measurements being used as the final measurement [30].

In accordance with this, we are going to measure the proportion of participants who will achieve systolic blood pressure ≤ 140 mmHg. There are several secondary outcomes to be investigated. Health-related quality of life baseline, 6 months, and 12 months after the intervention will be measured via the EuroQol 5-Dimension- 3-level (EQ-5D-3L) [31, 32]. The five dimensions include mobility, self-care, normal activities, pain or discomfort, and anxiety or depression. Each dimension has three levels: no difficulty, moderate problems, and serious problems. In addition, we are using the EQ-VAS to measure the patient’s self-rated health on a vertical visual analog scale, with two unique endpoints such as “Best imaginable health condition” for a score of 100 and “Worst imaginable health state” for a score of 0 [31].

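### Systolic blood pressure is not exempted from the telephone follow-up route, although the primary outcome is defined as a reading by a group-blind nurse; the double-blind label also needs correcting

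*Protocol article*

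**What the plan says.** **Primary outcome.** Under Outcome measures: "The primary outcome measure is the change in participants’ systolic blood pressure at 0, 6, and 12 months". On who takes it: "It will be recorded by a nurse who will be oblivious to the study participants’ group". The same section names a calibrated upper-arm mercury sphygmomanometer and asks for two readings, with a third if they differ by more than 5 mmHg. Data management repeats all of this.

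**Follow-up route.** Later in Data management: "At the end of the sixth and twelfth months, participants who completed the baseline survey in all four groups will be invited" to a study institute for interview, "or over the phone who will be unable to come to complete the second round of blood pressure measurement", with SEAMS, quality of life and pill count completing the list. Blood pressure is the first item. The document has no rule on how an SBP from a telephone contact would be obtained, flagged or analysed.

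**Missing data.** Statistical analysis plans a mixed-effects repeated-measures model for SBP, and multiple imputation at 12 months for data lost through attrition.

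**Blinding.** Under Study design: "It is a factorial randomized controlled trial with a superiority design and a double-blinding approach". The title and abstract use the same label. Randomization and blinding names data-collection and outcome-assessment staff as blinded, and Data management adds the biostatistician. Participants are not named as blinded anywhere.

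**The concern.** Participants know whether they attend counselling sessions, receive daily reminders, receive both or receive neither. The blinded nurse is therefore the main protection of the primary outcome against detection bias. If a participant who cannot attend may complete the blood-pressure item by telephone, the only value obtainable is one read out by the participant or a companion, from an unspecified device, by someone who knows the allocation. The outcome would then mix two kinds of measurement.

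The telephone route also covers month 12, the time point of the final analysis, so the ambiguity bears on the main result and not only on the 6-month visit.

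The label adds to the problem. A reader who takes double-blind to include participants would see less risk in a participant-reported value than there is.

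**Working it through.** **1. The two provisions side by side.**

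| | Outcome measures; Data management (measurement) | Data management (follow-up visits) |
|---|---|---|
| Who | Nurse unaware of group | Interviewer, in person or by telephone |
| Device | Named mercury sphygmomanometer | None stated for telephone contacts |
| Readings | Two, or three if they differ by more than 5 mmHg | None stated for telephone contacts |
| Time points | 0, 6 and 12 months | 6 and 12 months |

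A telephone contact can produce either a reported SBP or no SBP. In the first case the measurement definition is breached. In the second the follow-up sentence should exempt SBP, and it does not. The text needs correcting in both cases.

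**2. The plan's own sample size, as the reference point.** Inputs from Sample size: difference 148 − 143 = 5 mmHg, SD 18.5, two-sided 5%, power 90%, attrition 30%.

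- n per group = 2 × (1.960 + 1.282)² × 18.5² / 5² ≈ 288
- Inflated for attrition: 288 / (1 − 0.30) = 411.4, rounded up to 412
- Four groups: 4 × 412 = 1648

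This matches the stated 412 and 1648. Power with 288 analysed per group is 90.0%.

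**3. Possible bias (assumed inputs).** The document gives neither the share of SBP values that would come by telephone (f) nor any difference between arms in how telephone values are misreported (b). With both assumed, the shift in a between-group difference is f × b. The standard error with 288 per group is 18.5 × √(2/288) = 1.54 mmHg. The type I error is Φ(−1.96 + shift/SE) + Φ(−1.96 − shift/SE).

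| f | b (mmHg) | Shift (mmHg) | Share of 5 mmHg | Two-sided type I error |
|---|---|---|---|---|
| 0 | any | 0 | 0% | 5.0% |
| 10% | 5 | 0.5 | 10% | 6.2% |
| 20% | 5 | 1.0 | 20% | 9.9% |
| 30% | 10 | 3.0 | 60% | 49% |

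The first row applies if telephone contacts yield no SBP. The last row combines the two largest assumed values and is a corner case. The table shows how the error would scale; it is not an estimate for this trial.

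**4. Price of treating telephone-visit SBP as missing.** If these losses are additional to the 30% attrition, the number analysed per group is 412 × 0.70 × (1 − f), before any recovery of information by the model or imputation.

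- f = 10%: 412 × 0.70 × 0.90 ≈ 260, power about 87%
- f = 20%: 412 × 0.70 × 0.80 ≈ 231, power about 83%

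If telephone contacts already fall within the 30%, power stays at 90%. The document does not say which applies.

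**The case against.** The follow-up sentence is garbled and can be read the other way. The telephone may be only a mode of questioning, and the words about being unable to come may simply describe who is telephoned. On that reading SBP is missing at such visits, the nurse-measurement rule is intact, and the fix below is already intended. The schedule of assessments (Table 2), which that sentence cites, is not visible in the copy reviewed and may settle the matter. This objection stands in part. A reader might infer that the plan puts self-reported SBP into the primary outcome, but the document does not say that: it uses self-report language for adherence and pill counts, never for SBP. What remains is that the text permits such a value and has no rule against it. Nor does the imputation rule clearly apply, since it concerns attrition and a participant reached by telephone has not obviously been lost.

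A reader might also infer that telephone readings would favour the counselling arms, because their educational content includes "Information on hypertension, blood pressure self-monitoring, and frequent systolic blood pressure tests". That is possible but not established. Nothing says these participants receive a device, that the other arms lack one, or that reports would err in one direction.

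On blinding, the blinded parties can be identified from the text, and renaming the label changes no estimate. Both points are true. The label is still inaccurate as usually understood, because the arms are evident to participants.

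Unblinded self-report in the secondary outcomes is inherent to behavioural interventions and largely disclosed. Asking for a disclaimer there would be a preference and is not part of this point.

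**Conclusion.** The point holds as a conflict within the protocol. The follow-up text does not exempt SBP from the telephone route at 6 and 12 months, while the definition of the primary outcome requires a reading that only an attended visit can supply. As written, a participant-reported value could enter the primary analysis outside the blinded-assessor safeguard.

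The size of any bias cannot be determined from the document. It is zero if telephone contacts yield no SBP. Under the assumed shares and reporting differences it grows in proportion to both, and small shares do little harm. What matters is that nothing in the text limits the share. Separately, double-blind does not describe this design: assessors and the biostatistician are blinded, and participants are not and cannot be.

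**What to change.** In Data management, state that:

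- telephone contacts collect SEAMS, pill count and EQ-5D-3L/EQ-VAS only;
- only SBP taken by the blinded nurse under the Outcome measures procedure enters the primary analysis;
- SBP at a telephone visit is treated as missing and handled by the mixed model and the multiple imputation in Statistical analysis, with the imputation rule worded to cover these visits as well as attrition;
- contact mode is recorded at each follow-up visit.

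In the title, abstract and Study design, replace the double-blind label with a statement that outcome assessors and the biostatistician are blinded and participants are not.

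The cost is protocol wording, one extra data field, and more missing SBP values. It should not be assumed that these fit within the 30% attrition allowance; if they are additional, the power loss is the one worked out above. The expected telephone share should therefore be considered when the change is made.

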**Table 2 Tab2:**
[figure not shown]
Content for the schedule of enrolment, interventions, and assessments

There will not be a data monitoring committee for this trial. This study does not necessitate a data monitoring committee but instead, we have an epidemiologist, biostatistician, and clinician to assess study integrity and its design aspects during the course of the study.

Representatives of the sponsor, coordinator, and ethical review board will visit the study locations and conduct audits, including the verification of source data. Additionally, there will be three monitoring visits each.

### Dissemination and access

After the trial is completed, the study’s final findings will be published in a peer-reviewed journal and shared with participants, healthcare providers, and various research organizations via a public access database. The results will be posted on clinicaltrials.gov after it is completed.

The data will be kept highly confidential. None of the research staff (including research assistants, investigators, and clinicians) will have access to the data except the principal investigator and the members of the data monitoring committee.

### Reporting of adverse events

Reporting of significant adverse incidents that might plausibly happen as a result of the trial will not be included as primary or secondary outcomes. All adverse incidents that are voluntarily reported by participants, the study team, or medical professionals will be documented [35].

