	**mHealth intervention**	

The first group will receive no intervention and only standard hospital care (as per the practice of the hospital); the second group will receive monthly Ed-counselling sessions in addition to standard care; the third group will receive daily written and voice reminders and once weekly an education-led video in addition to standard care; the fourth group will receive Ed-counselling sessions every month, daily written and voice reminders, and once weekly an education-led video in addition to standard care.

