### Follow-up

Subjects in all four arms of the study will be followed up, three times in 12 months following recruitment. Blood pressure measurement for treatment outcome will be done. The Self-efficacy for Appropriate Medication Adherence Scale (SEAMS) is an adherence-monitoring scale that will be used to collect information from participants regarding their adherence to medication self-reporting. Apart from SEAMS, self-reporting pill counting for measuring medication adherence will be used, and health-related quality of life using EuroQol 5-Dimension-3-level (EQ-5D-3L) and a visual analog scale (EQ-VAS) will also be assessed. All the above assessments will be done at baseline, 6 months, and 12 months of follow-up.

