### Criteria for discontinuing or modifying interventions

Participants in the intervention groups will be contacted by phone by a member of our research team 1 month after the commencement of the intervention, and they will be interviewed. The interview will emphasize the participants’ satisfaction and comfort with the intervention. The study team will then be able to adjust the timing, duration, and frequency of some of the interventions or make further plans for adjustments.

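### Adverse events are described as voluntary reports while scheduled contact differs by arm, so any by-arm safety reading is at risk of ascertainment bias

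*Protocol article*

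**What the plan says.** The section Reporting of adverse events states that significant incidents plausibly due to the trial "will not be included as primary or secondary outcomes". It then gives the route into the record: "All adverse incidents that are voluntarily reported by participants, the study team, or medical professionals will be documented".

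The section Follow-up lists blood pressure, SEAMS, self-reported pill count, EQ-5D-3L and EQ-VAS, and adds: "All the above assessments will be done at baseline, 6 months, and 12 months of follow-up". Data management lists the same items for the 6- and 12-month rounds. Neither list has an adverse-event question. Follow-up also says "Subjects in all four arms of the study will be followed up, three times in 12 months following recruitment", which fits the 0, 6 and 12 month schedule only if baseline is one of the three.

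Study contact beyond these assessments depends on the arm:

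- Control: "The first group will receive no intervention and only standard hospital care" (Intervention, text after Table 1).
- All three intervention arms: "Participants in the intervention groups will be contacted by phone" one month after the start, for an interview about satisfaction and comfort (Criteria for discontinuing or modifying interventions).
- Ed-counselling and combined arms: face-to-face sessions led by doctors. The Abstract and the Intervention section make them monthly. Educational support with peer counseling gives four, at months 1, 4, 8 and 12. That same section says "all patients will be informed about antihypertensive medications, including indications, side effects, contraindications, warnings/precautions, drug interactions, and pregnancy risks", which in its place refers to patients who receive the counselling.

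The Interim analysis section has a 6-month review that covers, among other things, "any difficulties or negative outcomes associated with the administration of the intervention". It is internal and will not be reported.

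**The concern.** A volunteered report needs an occasion on which to volunteer it. Here the number of occasions is set by randomisation, and so is the number of times a doctor or team member, who may also report, sees the patient. The counselled arms have the most occasions and are the ones told what drug side effects look like. With identical true event rates, more events could be recorded in those arms than in control.

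The interventions aim to raise intake of antihypertensives in patients with coronary disease, so the control arm's rate is what shows whether a recorded excess is real. If that rate is collected with fewer chances to report, an excess in the counselled arms is hard to interpret, and a true deficit could be masked. This would affect any table of events by arm in the final report, and the 6-month review if it attributes negative outcomes to the intervention.

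**Working it through.** **Figures in the plan.** The article gives no adverse-event rate, reporting probability or contact count, so there is no safety figure to reproduce. The design figure reproduces: 2 × (1.960 + 1.282)² × 18.5² / 5² = 288 per arm, 288 / 0.70 = 412, and 4 × 412 = 1648. It plays no part below.

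**Step 1: scheduled contacts after baseline**, in months, with contacts in the same month counted once:

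| Arm | Months | Number | Ratio to control |
|---|---|---|---|
| Control | 6, 12 | 2 | 1 |
| mHealth | 1, 6, 12 | 3 | 1.5 |
| Counselled, four sessions | 1, 4, 6, 8, 12 | 5 | 2.5 |
| Counselled, monthly | 1 to 12 | 12 | 6 |

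Other ways of counting (baseline included or not, the call and coinciding visits counted separately or not) put the counselled-to-control ratio between 2.0 and 7.5. Outgoing reminders and videos are not counted as occasions to report.

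**Step 2: capture model.** Assumptions: the true rate is equal in all arms, an event falls uniformly over 0 to 12 months, and it is volunteered with probability p at each later contact. Then capture = average over event times of 1 − (1 − p)^k, where k is the number of contacts still to come.

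- Control: k = 2 for 6 months, then 1 for 6 months. At p = 0.1: (6 × 0.19 + 6 × 0.10) / 12 = 0.145.
- Counselled, four sessions: k = 5, 4, 3, 2, 1 for 1, 3, 2, 2 and 4 months. At p = 0.1: (0.4095 + 3 × 0.3439 + 2 × 0.271 + 2 × 0.19 + 4 × 0.10) / 12 = 0.230.
- Ratio: 0.230 / 0.145 = 1.59.

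The same steps for other values of p, over 12 months:

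| p | Control | mHealth (ratio) | Four sessions (ratio) | Monthly (ratio) |
|---|---|---|---|---|
| 0.1 | 0.145 | 0.152 (1.05) | 0.230 (1.59) | 0.462 (3.18) |
| 0.4 | 0.520 | 0.532 (1.02) | 0.665 (1.28) | 0.875 (1.68) |
| 0.8 | 0.880 | 0.883 (1.00) | 0.925 (1.05) | 0.979 (1.11) |

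**Step 3: up to the 6-month review.** Control has one contact (month 6), so capture is p. With four sessions the contacts are months 1, 4 and 6. At p = 0.1: (0.271 + 3 × 0.19 + 2 × 0.10) / 6 = 0.1735, a ratio of 1.73. At p = 0.4 the ratio is 1.46. With monthly sessions the ratios are 2.97 and 1.90.

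**Step 4: sensitivity to counting.** If coinciding contacts count separately, the 12-month ratios at p = 0.1 rise to 2.15 (four sessions) and 3.69 (monthly). The tables above use the more conservative count.

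**Step 5: with the fix.** If the comparison uses only answers to the same questions at months 6 and 12, each arm has two ascertainment points, and the ratio due to scheduled contact is 1.0 at any p.

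**The case against.** There are four serious points on the other side.

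*No by-arm safety analysis is stated.* Adverse incidents are not an outcome, and no test or table by arm is described. The Interim analysis section names neither the voluntary reports as its source nor a comparison of arms. A reader might infer that the 6-month review will judge safety by arm from these reports. The text does not say so. This stands, and it limits the point to any by-arm reading that is made.

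*Voluntary reporting may not be the sole route.* The article says such reports will be documented and does not exclude active questioning. The schedule in Table 2 is not shown, and a fuller protocol could hold more. This also stands as a caution. Still, the article has a dedicated section that names a method, and two itemised assessment lists without an adverse-event item, so this is a stated choice and not mere silence.

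*Contact outside the schedule is ignored.* All patients are registered in cardiology outpatient departments and receive standard care. Each hospital has a trial doctor and a focal research assistant, and medical professionals may report. These routes would shrink the ratios, by an amount the article does not allow one to calculate.

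*The effect depends on p.* For deaths and admissions known to the hospital, p may well be high and the distortion slight. A reader might infer that no real difference in admissions could be recognised. The p = 0.8 row does not support that. The problem lies mainly with events that are seldom volunteered, such as milder side effects or falls.

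**Conclusion.** The point holds as a risk. Collection as described is passive, scheduled contact is unequal by arm, and the arms with most contact are also taught about side effects. Any by-arm reading of adverse events is thus at risk of bias towards more recorded events in the Ed-counselling and combined arms.

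Under the model the false ratio to control is about 1.6, 1.3 and 1.05 at p = 0.1, 0.4 and 0.8 with four sessions, and 3.2, 1.7 and 1.1 with monthly sessions. These figures rest on an assumed p, uniform event times, equal true rates and no reporting outside scheduled contacts. The higher set also rests on the monthly schedule, which conflicts with the four-session schedule; the two passages must be reconciled. For mHealth alone the ratio is at most about 1.05 at 12 months, provided that its messages are not themselves a channel for reports.

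The stronger statement that the counselled arms will appear less safe is not supported, because the documents give neither a reporting probability nor a planned comparison. The systolic blood pressure outcome and the sample size are untouched.

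**What to change.** 1. At the existing 6- and 12-month assessments, by visit or phone, have the blinded interviewers ask all four arms the same short closed list for the time since the last assessment: hospital admission, cardiovascular event, fainting or fall, suspected drug side effect, and change of antihypertensive.
2. Take deaths, and admissions of patients who miss an assessment, from hospital records in the same way for every arm. Companions should not be the source: they attend the educational and counselling sessions, so relying on them could again favour the counselled arms. With 30% attrition planned, the missed assessments matter.
3. Base any arm comparison, and the 6-month review, on these items only. List volunteered reports, and anything raised in the 1-month call, separately without comparing arms.
4. Reconcile the monthly and four-session descriptions, so that the contact schedule by arm is known.

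The cost is about half a page added to questionnaires already given to everyone, one safety table, the record check, and a few minutes per interview. More events will be recorded overall. No new visit or larger sample is needed. Teaching about side effects could still colour answers to that one item; the event-based items are less open to this.
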